##### Cost-Effectiveness

The costs will be calculated from a societal perspective. The total costs of burn care will be calculated separately for each survivor of burn injuries in the preimplementation and postimplementation phases. The included cost categories will be health care costs and patients’ costs. Health care costs consist of burn center stay costs, treatment costs, clinical burn consultation costs, and outpatient burn care costs. Patient costs include travel costs, informal care costs, and productivity costs.

To evaluate the cost-effectiveness of the intervention, the complete EQ-5D-5L questionnaire will be used to compare the effectiveness in the control and intervention groups. The EQ-5D-5L questionnaire consists of 5 dimensions (mobility, self-care, daily activities, pain or discomfort, and anxiety or depression) and the EQ visual analog scale [37,50,54].

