### Strategies to Improve Adherence to Interventions: The BreeZe Implementation Approach

We will use the CFIR to develop a context-specific implementation approach for the BreeZe intervention and guide its application in each burn center [25]. Our main implementation strategies include education and training of health care professionals, enabling them to deliver the BreeZe intervention. This education and training will feature a blended approach that incorporates an electronic learning (e-learning) followed by an in-person training session.

The e-learning is divided into 3 parts, blending theory with interactive questions and videos. Part 1 features 2 short webinars. The first covers the key components and theoretical basis of self-management support, while the second focuses on the solution-focused conversation method and the introduction of the self-management web tool. Part 2 explains the structure and phases of providing self-management support through the BreeZe intervention with example videos. Finally, part 3 presents a practical application through a challenging case study of a patient struggling with a chronic condition, such as burns.

The content of the in-person training session builds on the e-learning. The in-person training session focuses on the practical application of the BreeZe intervention in routine clinical care. Burn physicians, aftercare nurses, and nurse practitioners will learn to activate survivors of burn injuries to generate their own solutions rather than focusing on the problems. They will also learn how to support survivors of burn injuries in achieving progression toward their goals in a short space of time. The training will consist of 3 blocks of 2 hours given on the same day and will be provided by a psychologist ([name]) together with a training actor. [name] was involved in the development and implementation of the ZENN intervention on which BreeZe is based [18]. In addition, there will be an online booster session after 2 months with the aim of discussing what the health professionals have encountered in their practice and optimizing standardization between health care professionals.

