###### Setting Level Outcomes – Cost-Effectiveness

Burn care costs will be calculated by multiplying the volumes of health care used by the corresponding unit prices. The unit prices were derived from the Dutch guidelines [62] and previous studies [63-65]. The unit prices of previous studies will be updated by the inflation correction of the current financial year. Substantive additions, for instance, patients’ costs will be based on previous studies and current care.

Utility values will be obtained from each patient with and without the BreeZe intervention by using the EQ-5D-5L questionnaire. The utility scores per domain range between 0 and 1, whereas 0 is death and 1 is perfect health. The total utility score per patient will be calculated. Quality-adjusted life years will be calculated by multiplying the length of time spent in a particular health state by its associated utility score.

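### The cost list has no category for BreeZe-only training and materials, which biases incremental cost in BreeZe's favour, and utilities are wrongly defined per EQ-5D-5L domain

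*Protocol article*

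**What the plan says.** **Costs.** The Cost-Effectiveness section under Outcomes sets the scope: "The costs will be calculated from a societal perspective". It then names the categories: "The included cost categories will be health care costs and patients’ costs". Both are broken down: "Health care costs consist of burn center stay costs, treatment costs, clinical burn consultation costs, and outpatient burn care costs", and "Patient costs include travel costs, informal care costs, and productivity costs". The Statistical Methods section (Setting Level Outcomes – Cost-Effectiveness) multiplies volumes by unit prices. It adds that further items, with patients' costs as the example, "will be based on previous studies and current care".

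**What BreeZe uses.** The section on the BreeZe implementation approach describes a three-part e-learning, then in-person training: "The training will consist of 3 blocks of 2 hours given on the same day and will be provided by a psychologist", together with an actor. An online booster follows after 2 months. Ancillary and Posttrial Care says that the researchers supply the webs and workbooks.

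**Utilities.** The same Statistical Methods section states: "The utility scores per domain range between 0 and 1, whereas 0 is death and 1 is perfect health". The next step is: "The total utility score per patient will be calculated". QALYs are then time in a health state multiplied by its utility. How domain scores become the total is not stated.

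**The concern.** A societal costing should count the resources that one group uses and the other does not. The cost list is worded as complete, yet training, e-learning, booster and materials have no place in it. All of them fall on the intervention side. An analyst who follows the list would understate the incremental cost of BreeZe.

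On the effect side, a scale from death to perfect health cannot describe one domain. Under the stated rule, a patient with no self-care problem would score as in perfect health on that domain while having the worst level of pain. QALYs built from such scores would not be on the scale on which cost per QALY is read.

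At stake is the cost-effectiveness result, a named secondary objective. The primary outcome is not affected.

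**Working it through.** The protocol states no cost, QALY or cost-effectiveness ratio, so there is no figure to reproduce.

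**Step 1. BreeZe resources set against the listed categories**

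| Resource | Where described | Listed category |
|---|---|---|
| Sessions in routine outpatient visits | BreeZe—Practical Application at Patient Level | Outpatient burn care |
| Added session around discharge, follow-up call | Same section | Can be counted as consultation or outpatient volume |
| Longer visits because of BreeZe | Not stated | Missed if each visit has a flat price |
| E-learning | BreeZe implementation approach | None |
| Training, 3 × 2 = 6 hours, psychologist and actor | Same section | None |
| Booster | Same section | None |
| Webs and workbooks | Ancillary and Posttrial Care | None |

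The unlisted items arise only in the intervention group. Leaving them out lowers that group's cost and leaves the control group's unchanged, so the direction of the bias does not depend on any assumed price.

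**Step 2. Illustrative size (assumptions, not in the documents)**

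Assume 10 to 30 staff; 10 hours each (6 training, 3 e-learning, 1 booster, of which only the 6 is documented); EUR 40 to 80 per hour; EUR 1,000 to 3,000 for trainer and actor at each of 3 centers; and EUR 10 to 50 of materials per patient.

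Cost per patient = (staff × hours × wage + 3 × trainer fee) / n + materials.

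- Low total: 10 × 10 × 40 + 3 × 1,000 = EUR 7,000
- High total: 30 × 10 × 80 + 3 × 3,000 = EUR 33,000

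| Denominator | Low | High |
|---|---|---|
| 53 (included, Results) | 7,000/53 + 10 = 142 | 33,000/53 + 50 = 673 |
| 89 (planned, Sample Size) | 7,000/89 + 10 = 89 | 33,000/89 + 50 = 421 |
| 1,000 (admissions per year, Patients With Burns; not all eligible) | 7,000/1,000 + 10 = 17 | 33,000/1,000 + 50 = 83 |

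The amount depends heavily on how one-off training is spread over patients, and the plan gives no rule for that.

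**Step 3. Range of the utility rule**

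- If the total is a sum: 5 domains × (0 to 1) = 0 to 5. A year in full health gives 5 × 1 = 5 QALYs, against 1 × 1 = 1 for a single index. Compared with the mean of the same scores, every QALY difference is 5 times larger and every cost per QALY 5 times smaller.
- If it is a mean: the range is 0 to 1, but five equally weighted item scores are not a preference-based value of the health state, and a state valued below 0 cannot occur.
- If it is a single index for the whole profile: the anchors and the time-multiplied-by-utility step are right, but the words about domains are then wrong.

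Table 1 gives the EQ-5D-5L a range of 5 to 25 in the cost-effectiveness row, which is five items scored 1 to 5 and added. That hints at an additive reading but does not establish one.

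**The case against.** **Training is implementation, not delivery.** The protocol classes education and training as implementation strategies. They are one-off, and the materials stay with the centers. Whether set-up belongs in a per-patient cost is a scope choice. This stands in part: it is why the spreading rule and a result without these costs are needed. It does not justify a list that drops them unannounced under a societal perspective.

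**The wording on additions leaves room.** Its only example is patients' costs, so it cannot be relied on to bring in intervention costs.

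**The utility sentence is loose wording for the usual index, and the value set belongs in an analysis plan.** This may well be the intention, and an unnamed value set would not by itself be a finding in an article. The sentence as printed, however, states a wrong definition.

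A reader might also infer more than the documents support:

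- *That delivery of BreeZe is charged nothing.* Sessions run mainly within outpatient appointments, and added contacts can be counted as volumes.
- *That the cost difference will favour BreeZe.* One component is understated; the sign of the whole is unknown.
- *That patient costs have no instrument, so the perspective must be restated.* Table 2 has the return-to-work instrument at 6 and 12 months, and travel can be derived from visits. Only informal care lacks an obvious measure, which the full protocol may supply. The reference to previous studies sits among sentences on unit prices and need not mean that volumes are imported.
- *That the burn center stay must come out.* It precedes most of BreeZe and adds variability, but total burn care cost is the stated quantity. Keeping the stay is a trade-off.
- *That QALYs will run to 5.* That holds only if the total is a sum.

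**Conclusion.** The point holds in two places and should be corrected before analysis starts in August 2026.

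1. The cost list leaves out training, e-learning, booster and materials, and any added professional time within a visit if a flat visit price is used. This biases the incremental cost in BreeZe's favour. Size and final sign cannot be computed from the documents. The euro ranges above rest wholly on my assumptions and show only that the choice of denominator matters.
2. The utility definition is wrong as printed. Neither a sum nor a mean of domain scores gives a valid QALY. The factor of 5 applies to the sum alone. If a whole-profile index is intended, the error is one of wording and the QALY step is sound.

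**What to change.** **Costs.** Add an intervention-cost category charged to the intervention group: e-learning, training (staff hours, psychologist, actor), booster, materials, and added professional time within visits where a flat price would miss it. State how one-off training costs are spread over patients, and report results with and without them. Reporting the index admission cost separately is at most an optional sensitivity analysis.

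**Utilities.** Replace the domain and total sentences with one index per patient per occasion, taken from the complete EQ-5D-5L profile with a named value set (Dutch, given the setting), allowing values below 0. Define QALYs as the area under the curve over T1, T2 and T3.

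**Cost of the change.** Wording, plus modest collation of invoices and staff hours. Centers already track training attendance and e-learning completion (RE-AIM: Implementation), and the EQ-5D-5L is already scheduled at all three occasions, so no new patient data are needed. The result may look less favourable to BreeZe.

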### RE-AIM: Adoption

Adoption of the intervention will be measured at the staff and setting level. At the staff level, we will assess whether the intervention is adopted by conducting CFIR-informed interviews with burn physicians, nurse practitioners, and aftercare nurses, by asking if they use the BreeZe intervention in their daily work. These interviews will provide working hypotheses to explain the degree of individual intervention adoption. At the setting level, we will assess whether the BreeZe intervention is used within an individual burn center.

### RE-AIM: Implementation

The implementation of BreeZe will be evaluated by assessing the intervention’s fidelity to the core components of BreeZe (eg, goal setting, action planning, and motivational interviewing), implementation fidelity to the implementation strategies (eg, completing the e-learning, attending the training, and being exposed to the additional ERIC implementation strategies), and the adaptations made to BreeZe or to the burn center (eg, workflows).

To gain insight into the intervention fidelity to the core components, health care professionals will be asked to document in patient records when they have used certain components. A convenience sample will be taken by assessing patient records to investigate how often the core components were used.

To gain insight into the implementation fidelity to the implementation strategies, each burn center will be asked to keep track of the completion of the implementation plan, including the staff attendance to the training plan and their e-learning completion rate.

To gain insight into the adaptations made to BreeZe or to the burn center (eg, workflows), adaptations will be documented using the Framework for Reporting Adaptations and Modifications-Enhanced (FRAME) during the postimplementation phase [43].

In addition to assessing the degree of adoption, the CFIR-informed interviews with burn physicians, nurse practitioners, aftercare nurses, and burn center managers will also be used to provide working hypotheses to explain implementation success or failure.

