**Methods:**

This multicenter study in the Netherlands is an implementation-effectiveness hybrid type 2 study, with a nonrandomized stepped-wedge design. Starting April 2024, 3 phases have been sequentially rolled out across the 3 specialized Dutch burn centers over a period of 20 weeks—the preimplementation phase (usual care), implementation phase, and postimplementation phase. To identify barriers and facilitators of implementation, the Consolidated Framework for Implementation Research (CFIR) will be used. For evaluation, the Reach, Effectiveness, Adoption, Implementation, and Maintenance (RE-AIM) evaluation framework is used. The coprimary outcomes are (1) self-management skills and (2) the implementation outcomes are reach, adoption, implementation, and maintenance. Secondary effectiveness outcomes are self-regulation, participation, dependency, patient-centeredness for survivors of burn injuries, self-management support skills for health care professionals, and cost-effectiveness. Data collection for survivors of burn injuries occurs at 2 weeks, 6 months, and 12 months post discharge, using questionnaires. Data collection for health care professionals occurs before training and 3, 6, and 12 months post implementation, using questionnaires, video observations, and interviews. Data analysis will include both quantitative and qualitative methods for comprehensive evaluation.

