##### BreeZe—Practical Application at Patient Level

The start of BreeZe depends on the health care trajectory of the survivor of burn injuries. For survivors of burn injuries who were admitted for a 1-day stay at a burn center for a debridement or skin graft surgery, BreeZe will commence ±7 to 14 days after discharge, and the steps of BreeZe will be divided into 4 sessions. For survivors of burn injuries who were admitted for more than 24 hours at a burn center, an extra session is added, which will take place around the day of discharge. It is important to note that the number of outpatient consultations needed to progress through these sessions depends on the needs for self-management support of the survivor of burn injuries and the logistical constraints of the burn center. Hence, a fixed intervention timeline cannot be specified. In case one or more informal caregivers are involved, they will also be offered the opportunity to be engaged from the start.

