### Outcomes

#### Overview

To translate our intervention into practice, we adhere to the RE-AIM framework [26,27]. The RE-AIM framework consists of 5 dimensions—reach, effectiveness, adoption, implementation, and maintenance. We have presented each outcome measure under its RE-AIM dimension in Table 1. Detailed information on the definitions of the RE-AIM dimensions and their related measures can be found in Multimedia Appendix 1.

**Table 1. T1:** Overview of the outcome measures categorized by each RE-AIM^a^ dimension.

Outcome	Instrument	Number of questions	Number of domains	Answer scale	Minimum-maximum score
Coprimary outcome effectiveness measure					
Self-management skills	Partners in Health scale [34]	12	2	9-point Likert scale	0‐96
Secondary outcome effectiveness measures – survivor of burn injuries level					
Self-regulation	Self-Regulation Assessment [35]	22	4	5-point Likert scale	0‐110
Participation	Measure of Experiential Aspects of Participation [36]	4	4	5 answer options	—^b^
Daily activities	EuroQol-5D-5L [37]	1	—	5-point Likert scale	1‐5
Self-care	EuroQol-5D-5L [37]	1	—	5-point Likert scale	1‐5
Dependency	New formulated question	1	—	5-point Likert scale	1‐5
Return to work or school	Adjusted International Consortium for Health Outcomes Measurement [38]	3	—	5 answer options	—
Patient centeredness	American Consumer Assessment of Health Plan Survey [39]	5	—	4-point Likert scale	0‐20
Secondary outcome effectiveness measures – health care professional level					
Self-management support skills	Self-Efficacy and Performance in Self-management Support [40]	36	6	5-point Likert scale	0‐180
Need-supportive counseling	Coding and Observing Need-Supportive Counseling in Chronic Care Encounters [41]	44	9	5-point Likert scale	0‐24
	Nurse-Child Interaction Taxonomy [42]	16	3	Percentages	0%‐100%
Secondary outcome effectiveness measures – setting level					
Cost-effectiveness	EuroQol-5D-5L [37]	6	5	5-point Likert scale Visual Analog Scale	5‐25 0‐10
Coprimary outcome implementation approach measures					
Reach	Dutch Burn Repository R3	—	—	Frequencies and percentages	—
Reach	Project coordinator records	—	—	—	—
Reach	Screening form	—	—	—	—
Reach	CFIR^c^-informed interviews	—	—	—	—
Adoption (staff level)	CFIR-informed interviews	—	—	—	—
Adoption (setting level)	Project coordinator records	—	—	—	—
Intervention fidelity	Electronic patient records	—	—	Frequencies and percentages	—
Intervention fidelity	Project coordinator records	—	—	—	—

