### RE-AIM: Implementation

To assess intervention fidelity, health care professionals are asked to document in patient records if, when, and which components of the BreeZe intervention they have used (eg, the Self-management web, goal setting, and action planning). This documentation will be used to assess how often certain components are used.

To assess implementation fidelity to the implementation strategies, the results of the implementation plan will be analyzed and presented with descriptive statistics (eg, completing the e-learning, attending the training, and being exposed to the additional ERIC implementation strategies).

Furthermore, to gain insight into the adaptations made to BreeZe or to the burn center (eg, workflows), we analyze the adaptations that have been documented during the study. These results will be schematically presented and summarized in text.

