### Methods for Additional Analyses

Our analyses, as described above, are based on an intention-to-treat approach. If survivors of burn injuries did start with the BreeZe intervention but did not complete it as intended, this will be documented. In case this occurs, we will perform additional analyses conforming to this protocol using only the subgroup of survivors of burn injuries who received and/or used at least 2 BreeZe components (eg, workbook and self-management web).

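### Intervention fidelity, a coprimary implementation measure, is to be read from a convenience sample of records when all 53 intervention patients could be read

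*Protocol article*

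**What the plan says.** The Abstract (Methods) names the coprimary outcomes as self-management skills and, second, "the implementation outcomes are reach, adoption, implementation, and maintenance". In Table 1, intervention fidelity stands under the heading "Coprimary outcome implementation approach measures". Three sources are listed for it: electronic patient records (reported as frequencies and percentages), project coordinator records, and CFIR-informed interviews.

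Three sections bear on the record source:

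- **Outcomes, RE-AIM: Implementation.** "health care professionals will be asked to document in patient records when they have used certain components". Then: "A convenience sample will be taken by assessing patient records to investigate how often the core components were used".
- **Statistical Methods, RE-AIM: Implementation.** Professionals document which components they used and at what point. "This documentation will be used to assess how often certain components are used". No sample is mentioned.
- **Methods for Additional Analyses.** If patients start BreeZe but do not complete it as intended, this is to be documented, and a further analysis is run "using only the subgroup of survivors of burn injuries who received and/or used at least 2 BreeZe components".

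The Results section reports 53 participants in the intervention group and 42 in the control group.

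**The concern.** A convenience sample has no known selection probabilities, so a percentage from it need not describe the intervention group. Records may be picked because they are complete, recent, from one center, or kept by an engaged professional. The Study Setting section says the centers differ in professional roles and autonomy in aftercare, so an uneven mix of centers could by itself move the figure.

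The fidelity figure has a job to do. In Methodological Considerations the authors argue that, unless implementation is assessed, a success or failure cannot be attributed to the intervention or to its delivery. If the PiH comparison is inconclusive, readers will look to fidelity to explain it. A figure that is too high would favour reading BreeZe as delivered but ineffective. One that is too low would favour reading it as not delivered.

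The subgroup analysis has a separate need. Its trigger (started but not completed) and its membership rule (at least 2 components) both require component receipt to be known patient by patient.

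**Working it through.** **Plan's own figure.** The article attaches no sample size, precision or target to fidelity, so there is nothing to reproduce.

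**Sections side by side.** The Outcomes section reads a sample of records. The Statistical Methods section uses the documentation without mentioning a sample. Methods for Additional Analyses needs a count of components for each intervention patient. The first two do not state the same denominator, and none of the three says that component receipt will be extracted for every intervention patient.

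**Illustration.** Input from the article: N = 53 intervention patients (Results). Assumed, because the article gives neither: the number of records read, m, and the share showing use. It is also assumed that the records come from these 53 patients.

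1. Patients left unclassified for the subgroup from this source, N − m:
   - m = 20: 53 − 20 = 33 (62%)
   - m = 27: 53 − 27 = 26 (49%)
   - m = 40: 53 − 40 = 13 (25%)
   - m = 53: 0

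2. Bounds on use among all 53 when x of m records show use and nothing is assumed about the rest, x/N to (x + N − m)/N:
   - m = 20, x = 16 (80%): 16/53 = 30% to 49/53 = 92%
   - m = 40, x = 32 (80%): 32/53 = 60% to 45/53 = 85%

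3. Effect of selection. If records showing use are k times as likely to be picked and true use is p, the expected observed share is pk/(pk + 1 − p). With p = 0.6:
   - k = 2: 1.2/(1.2 + 0.4) = 75%
   - k = 0.5: 0.3/(0.3 + 0.4) = 43%

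The article gives no ground for choosing k above or below 1, so the direction is open. A margin of error from the random-sampling formula (for m = 20, 1.96 × √(0.25/20) × √(33/52) = 17.5 points) does not apply to a convenience sample and is not relied on here.

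**The case against.** The strongest reply has five parts.

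- **The sample is not the only source.** Table 1 also lists project coordinator records and interviews. This stands, and the point is confined to the record-based percentages.
- **The subgroup is never tied to the sample.** A reader might infer that the sections contradict each other and that the subgroup cannot be formed. The article does not support this. Professionals are asked to document components generally, incomplete delivery is to be documented, and the subgroup analysis is additional and conditional. The per-patient data may well exist. What is absent is a statement that they will be extracted for everyone.
- **Upward bias is not shown.** A reader might infer that records with BreeZe entries are easiest to find, so fidelity will look too good. No section says so, and under-documentation would push the figure down.
- **Details may lie elsewhere.** Size, frame and selection rule may be in the full protocol or in Multimedia Appendix 1, so their absence is not the complaint. The choice of a convenience sample is stated in the article and is the complaint.
- **The frame may be wider than the 53.** BreeZe is applied in routine care. If the sample is drawn from all aftercare patients, the bounds above do not carry over. The case for reading the enrolled patients remains, because the effectiveness comparison is made on them.

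None of this favours a convenience sample over a full read of so small a group.

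**Conclusion.** The concern holds in limited form. A coprimary implementation measure rests, for its record-based percentages, on a sampling method open to selection of unknown direction. The statistical section describes the same measure without that sample. No stated procedure yields component receipt for every intervention patient, which the conditional subgroup needs.

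The size of any bias is unknown. The figures of 33 unclassified patients and of 30% to 92% depend on an assumed 20 records drawn from the 53, and the second also on an assumed 80% observed use. They show how little a small sample would settle, not what will happen. Fidelity is descriptive, and the intention-to-treat PiH comparison does not depend on it. The change is still worth making, because the group is small, professionals are already asked to document component use, and a full read removes both sampling error and record selection.

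**What to change.** In the Outcomes section on RE-AIM: Implementation, replace the sentence on the convenience sample with wording such as:

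> Use of each core component will be abstracted from the patient records of all enrolled intervention participants (n=53) and reported as frequencies and percentages, overall and by center.

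Then:

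- State the same denominator in the Statistical Methods section on RE-AIM: Implementation.
- State in Methods for Additional Analyses that the subgroup is formed from this extract.
- Optionally, add session counts by care track. The article says "the steps of BreeZe will be divided into 4 sessions" for one-day stays, with an extra session after longer admissions. Its fidelity definition is by components, so this is not required.

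**Cost.** Some hours of record reading (33 more records than an assumed sample of 20) and a check that consent covers the extraction, since the consent forms are not shown. The fidelity figure may become less favourable. Incomplete documentation by professionals would remain and should be reported as a limitation. Follow-up ends in July 2026 and analysis starts in August 2026, so the change can be recorded before analysis begins.
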